### Outcomes

2.5

The primary outcome of the study is the severity of RIOM, assessed using RTOG grading scale. This will be measured as the proportion of participants who develop severe oral mucositis (RTOG grade ≥ 3) at any time during radiotherapy and up to six weeks following completion of radiotherapy, compared between the two study arms. The primary outcome will be assessed from randomisation until the last day of study medication use.

The secondary outcomes include oral mucositis severity assessed using WHO oral mucositis scale, measured as the proportionate reduction in the occurrence and severity of mucositis during radiotherapy and up to six weeks post-radiotherapy. Oral cavity pain, evaluated using VAS as the proportion of participants achieving a minimum two-point reduction in pain intensity and analgesic usage, assessed as the percentage of participants requiring analgesics categorised according to WHO three-step analgesic ladder. Safety outcomes will be evaluated by documenting the number of adverse events reported in each study group. Treatment interruption will be assessed as the proportion of participants experiencing one or more radiotherapy interruptions due to severe RIOM and the total number of days of missed radiotherapy. In addition, body weight changes during radiotherapy, requirement for nasogastric tube feeding, and interruptions in oral intake will be documented as exploratory indicators of nutritional impact. All secondary outcomes, except treatment interruption, will be assessed from randomisation until the last day of study medication use, while treatment interruption will be evaluated until the completion of radiotherapy.

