### Objectives

1.3

The primary objective of this study is to evaluate the proportionate reduction in the occurrence of severe RIOM, as assessed using RTOG grading scale, among participants receiving a Siddha regimen as an adjunct to standard care compared with those receiving standard care alone, assessed during radiotherapy and at six weeks post-radiotherapy.

The secondary objectives are to assess the proportionate reduction in the severity of radiation-induced oral mucositis using WHO oral mucositis scale at the same time points; to compare oral cavity pain intensity between the study groups using VAS, assessed weekly throughout the study period; to evaluate changes in analgesic usage, including escalation or de-escalation according to the WHO Three-Step Analgesic Ladder, on a weekly basis during the study period; to estimate and compare the proportion of adverse reactions between the study groups; and to evaluate differences in the frequency and duration of treatment interruptions attributable to oral mucositis between the study groups.

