#### Inclusion criteria

2.3.1

Participants aged 20–75 years of any gender, diagnosed with head and neck cancers involving the oral cavity and/or oropharynx and scheduled to undergo radiotherapy for a period of 4–7 weeks with a total radiation dose of 55–72 Gy, will be eligible for inclusion in the study. Only those who are willing to participate and are willing to provide written informed consent before the enrolment, will be included.

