#### Comparator description

2.4.2

Participants in Arm B will receive SOC alone for the management of RIOM, as described in the intervention arm. Additional topical anaesthetic and anti-inflammatory gels will be provided for oral mucositis of grade ≥ 2 in accordance with institutional protocol.

Assessments will be conducted weekly, in parallel with the intervention arm, until 6week post radiotherapy or until recovery, whichever occurs earlier. Treatment adherence will be monitored by the oral hygiene coordinator, staff nurse, and investigators, with family caregivers trained during the radiotherapy admission period to assist in monitoring during the post-radiotherapy phase. Trial interventions will be administered for 10–13 weeks, depending on the required radiation dose (Gy) based on tumour size and severity. Recovery will be defined as Grade 0 oral mucositis on both RTOG and WHO oral mucositis scales. All participants will receive radiotherapy using a linear accelerator (LINAC) with three-dimensional conformal radiotherapy (3DCRT) for a duration of 4–7 weeks, in accordance with institutional practice. Before initiation of radiotherapy, all participants will undergo a baseline oral examination and receive necessary dental care, wherever feasible, according to institutional standard dental care protocols. Standardized oral hygiene instructions will be provided and reinforced uniformly throughout the study period in both study arms.

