### Participant timeline

2.6

Participants will undergo initial screening and randomisation at baseline, followed by a 14-week observation period comprising weekly clinical evaluations and periodic laboratory assessments as detailed in the timeline below (Table 2).

**Table 2 T2:** Schedule of enrolment, interventions, and assessments.

Activity/Assessment	Baseline	W1	W2	W3	W4	W5	W6	W7	W8	W9	W10	W11	W12	W13
Enrolment														
Screening & Informed Consent	X													
Randomisation & Allocation	X													
Intervention														
Study Intervention	X	X	X	X	X	X	X	X	X	X	X	X	X	X
Efficacy Assessment														
RTOG Scale	X	X	X	X	X	X	X	X	X					X
WHO oral mucositis Scale	X	X	X	X	X	X	X	X	X	X	X	X	X	X
VAS		X	X	X	X	X	X	X	X	X	X	X	X	X
WHO 3-step analgesic ladder		X	X	X	X	X	X	X	X	X	X	X	X	X
Interruption of RT		X	X	X	X	X	X	X	X					
Days of Missed RT		X	X	X	X	X	X	X	X					
Safety & Laboratory Assessment														
Safety Monitoring		X	X	X	X	X	X	X	X	X	X	X	X	X
CBC	X								X					X
LFT	X								X					X
RFT	X								X					X

RT, radiotherapy; RTOG, Radiation Therapy Oncology Group; WHO, World Health Organization; VAS, visual analogue scale; CBC, complete blood count; LFT, liver function test; RFT, renal function Test; W1−13, No. of week.

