### Ancillary and post-trial care

6.5

After completion of RT period, participants in both study arms will be followed for an additional 6weeks, during which the assigned treatments will be continued. Follow-up assessments will be conducted weekly via telephone to monitor recovery and document relevant outcomes.

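### The primary outcome window and the RTOG schedule contradict each other, and as printed only a 7-week radiotherapy course has an RTOG assessment at its own six-week point

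*Protocol article*

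**What the plan says.** The protocol article gives several accounts of when the primary outcome is measured.

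- **Section 2.5 (Outcomes):** RTOG grade 3 or worse "at any time during radiotherapy and up to six weeks following completion of radiotherapy, compared between the two study arms". The same paragraph adds: "The primary outcome will be assessed from randomisation until the last day of study medication use".
- **Sections 1.3 (Objectives) and 2.2 (Trial design):** RTOG during RT plus one later time point. Section 1.3 has it "assessed during radiotherapy and at six weeks post-radiotherapy".
- **Section 4.1 (assessment and data collection):** the grade distributions of all four scales, RTOG among them, are to be examined every week of the study.
- **Table 2 (section 2.6):** the RTOG row reads "RTOG Scale X X X X X X X X X X". The ten marks stand under baseline, W1–W8 and W13, and W9–W12 are blank. The row below it reads "WHO oral mucositis Scale X X X X X X X X X X X X X X", which is every column.

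Two further statements fix the calendar. Section 2.3.1 admits patients "scheduled to undergo radiotherapy for a period of 4–7 weeks with a total radiation dose of 55–72 Gy", and section 2.4.2 says "Trial interventions will be administered for 10–13 weeks".

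On how participants are seen after RT, section 6.5 says: "Follow-up assessments will be conducted weekly via telephone to monitor recovery and document relevant outcomes". Section 4.1 also describes this follow-up as telephonic. Section 2.4.3, however, counts leftover medicine packs at follow-up visits, section 4.2 has reminder calls before scheduled visits, section 4.3 records post-RT visit dates in a diary, and Table 2 places blood tests at W8 and W13.

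**The concern.** An outcome of the form 'ever grade 3 or worse' can only be as complete as the assessments behind it. Here the window in section 2.5 runs continuously to six weeks after RT, but the schedule leaves a four-week hole in the RTOG row. The schedule also counts calendar weeks from baseline, while the window is tied to the end of RT, which differs between participants. Follow-up for the primary endpoint therefore depends on RT length, and two analysts following different sections could classify the same participant differently.

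Contact mode adds to this. Grade 3 by its mucosal sign, and grade 4 (ulceration, haemorrhage or necrosis), have to be seen. Section 3.4 protects an open-label trial through assessors unaware of allocation who examine the participant at a visit, and the Discussion relies on that protection. A grade taken by telephone rests on the report of a participant who knows the allocation.

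Section 2.4.2 also ends assessment at recovery, defined as grade 0 on both RTOG and WHO scales. That rule cannot be applied in weeks when RTOG is not graded.

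**Working it through.** **Inputs.** RT length L = 4 to 7 weeks (section 2.3.1); follow-up of six weeks after RT (section 2.5); RTOG weeks after baseline = {W1–W8, W13} (Table 2).

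**Reproducing the plan's own figure.** Total duration = L + 6 = 10, 11, 12 or 13 weeks. This matches the 10–13 weeks in section 2.4.2 and Table 1, so the Table 2 week grid and the post-RT window can be laid over each other.

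**Crossing the window with the schedule.** Post-RT weeks are W(L+1) to W(L+6); the six-week point is W(L+6).

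| RT length | Post-RT weeks | RTOG marked | RTOG blank | Six-week point | RTOG there? |
|---|---|---|---|---|---|
| 4 weeks | W5–W10 | W5–W8 | W9–W10: 2/6 = 33% | W10 | No |
| 5 weeks | W6–W11 | W6–W8 | W9–W11: 3/6 = 50% | W11 | No |
| 6 weeks | W7–W12 | W7–W8 | W9–W12: 4/6 = 67% | W12 | No |
| 7 weeks | W8–W13 | W8, W13 | W9–W12: 4/6 = 67% | W13 | Yes |

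**The W13 cell for shorter courses.** Study medication ends at W10, W11 or W12, so W13 falls 13 − 10 = 3, 13 − 11 = 2 or 13 − 12 = 1 week later. Section 2.5 closes the assessment period on the last day of medication. Read literally, the W13 grade lies outside the primary outcome for 4-, 5- and 6-week courses, and even the narrower timing in section 1.3 has no scheduled measurement for them.

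**Is the gap an extraction fault?** Probably not: the WHO, VAS and analgesic-ladder rows of the same table are marked every week to W13.

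**What a telephone contact can establish.** Table 3 gives RTOG grade 3 two limbs: a confluent fibrinous mucosal finding, or severe pain needing narcotic analgesics. The second can be reported by telephone, and pain score and analgesic step are scheduled weekly to W13. The first limb, and all of grade 4, cannot be confirmed without looking.

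**The case against.** A reader might infer that the outcome cannot be observed for most of the post-RT period. The documents do not support that.

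- On the schedule alone, the unassessed share exceeds half only for 6- and 7-week courses. It is half for five weeks and a third for four.
- In-person contact after RT is not ruled out. Sections 2.4.3, 4.2 and 4.3 refer to visits, and the blood tests at W8 and W13 share columns with the last two RTOG marks. What stands is that contact mode is described inconsistently.
- Part of RTOG grade 3 can be captured by telephone, as shown above.
- The outcome is cumulative. Weekly RTOG to W8 covers all of RT for every course length and at least one week beyond it. Section 1.1 places peak severity at 66–70 Gy, towards the end of RT, so many first severe grades should fall in covered weeks. The scheduling gap is also the same in both arms.
- Table 2 may be a template for the longest course, with W13 meant as 'six weeks after RT' for everyone. That is plausible, since sections 1.3 and 2.2 tie the assessment to the end of RT, but the table as printed does not say so.

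These points limit the likely damage. They do not remove the conflict between section 2.5, sections 1.3 and 2.2, section 4.1 and Table 2. Nor is this detail left to a fuller document: the article itself prints the window, the grid and the contact mode, and they disagree.

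**Conclusion.** The primary endpoint cannot be collected as section 2.5 defines it under the schedule in Table 2. RTOG is unscheduled in 2, 3, 4 and 4 of the six post-RT weeks for RT of 4, 5, 6 and 7 weeks. As printed, the six-week RTOG exists only for a 7-week course. Whether post-RT grades come from an allocation-blind examination is not settled.

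The counts assume whole-week courses, W1 as the first week of RT, and Table 2 read literally. If W13 is meant to float with the end of RT, the six-week point is covered, but the 'any time' wording still lacks assessments in between.

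The effect on the result cannot be computed. The article gives no share of first grade 3 or worse events arising after W8, and that share may be small. The case for acting is that the definition must be unambiguous and that recruitment is under way (section 2.8): an examination not done cannot be recovered later.

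**What to change.** 1. Anchor Table 2 to each participant's last RT fraction.
2. Keep every RTOG assessment already scheduled through W8. Examining only to the end of RT plus one six-week visit would leave 5 of 6 post-RT weeks unassessed for everyone, worse than the present table.
3. Move the W13 RTOG visit to end of RT plus six weeks (W10–W13) for every participant, in person with the allocation-blind assessor.
4. Define the primary outcome as RTOG grade 3 or worse at any in-person assessment in that schedule, with telephone grades as supportive or sensitivity data only.
5. Make sections 1.3, 2.2, 2.5, 4.1, 6.5 and Table 2 agree, and reconcile the stop-at-recovery wording in sections 2.4.1 and 2.4.2 with the six-week visit.

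**Result.** Post-RT weeks without RTOG become W9 (1 of 6) for a 4-week course, W9–W10 (2 of 6) for five, W9–W11 (3 of 6) for six and W9–W12 (4 of 6) for seven. Every course then has its six-week point.

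**Cost.** An amendment that re-times an existing visit. No extra attendance arises if the blood tests in the same column are taken at that visit, which is for the team to decide. Post-RT assessments up to W8 (four, three, two and one for 4-, 5-, 6- and 7-week courses) must be attended to count; if any are now telephone contacts, those visits are an added burden. Severe episodes that begin and resolve between the last weekly examination and week six after RT will not be counted, so the conclusion should speak of severe mucositis seen at scheduled examinations rather than at any time.

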#### Criteria for discontinuing or modifying allocated interventions

2.3.3

Participants may be withdrawn from the study prior to completion if they withdraw informed consent at any time without providing a reason, develop serious or intolerable adverse reactions, or experience worsening of RIOM or the emergence of other medical conditions requiring treatment that is incompatible with continued study participation. Participants may also be withdrawn in cases of repeated non-adherence to study procedures, scheduled visits, or the medication regimen, defined as less than 70% drug compliance despite counselling, or if they are unable to be contacted for scheduled assessments despite reasonable efforts.

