#### Intervention description

2.4.1

Arm A will constitute the intervention group, in which participants will receive the Siddha regimen as an adjunct to SOC during the entire course of radiotherapy and the post-radiotherapy period. Participants will be assessed weekly throughout the study duration or until complete recovery from oral mucositis, whichever occurs earlier.

***Procurement of trial drugs:*** The interventional drugs will be procured from GMP certified manufacturers. TPC will be procured from TAMPCOL, Chennai and GV will be procured from IMPCOPS, Chennai.

***Method of drug administration:*** The Siddha intervention will consist of TPC mouthwash and topical application of GV, administered as follows. TPC mouthwash will be prepared using pre-measured teabags, each containing 2 g of TPC. Participants will be instructed to immerse one teabag in 60 mL of freshly boiled water and allow it to stay immersed for 10–15 min, until the solution cools to room temperature. The teabag will then be removed, and the resulting solution will be used immediately as a mouth rinse. Fresh preparation will be performed prior to each use. Then, participants will be instructed to rinse with 60 mL of the mouthwash at each time point, three times daily after meals, swishing for 30seconds and then spitting out the solution. The mouthwash regimen will commence on day0 (one day prior to initiation of radiotherapy) and will continue during radiation therapy and 6weeks post radiation therapy. In addition, GV will be administered at a dose of 10 g per day, applied topically within the oral cavity three times daily, following mouth rinsing. Depending on the clinical schedule, treatment may be initiated on the same day as radiotherapy in some participants.

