### Data management

4.3

All study-specific data will be recorded in standardised CRFs. Source documents, including medical records and laboratory reports, will be maintained to allow verification of recorded data. Investigators will document all required participant information in the CRFs, with appropriate justification for any missing data. Data recorded in the CRFs will be routinely cross-verified against source documents, and any discrepancies will be addressed and resolved through data clarification. Treatment details, follow-up information, and scheduled visit dates during post-RT period will be documented in a patient diary. Protocol deviations and the use of concomitant or rescue medications, if any, will also be recorded in the CRFs and reviewed by the investigators at each visit.

Participants who discontinue or deviate from the intervention protocol will continue to be followed, and their data will be included in the final analysis in accordance with the *intention-to-treat* principle. To support participant retention and ensure complete follow-up, regular telephonic communication will be maintained.

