Efficacy analysis will follow a modified *intention-to-treat* approach, including all randomised participants who have undergone at least one post-baseline assessment. Safety analysis will be performed using the per-protocol population. A two-sided *p* value of ≤0.05 will be considered statistically significant. All statistical analyses will be carried out by a statistician using the Statistical Package for the Social Sciences (SPSS) software.

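### Section 2.5 gives the primary outcome two different windows, and the one tied to study medication would count a first severe grade after early stopping as no event

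*Protocol article*

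**What the plan says.** All references are to the Protocol article.

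- **2.5 Outcomes, fixed window.** The primary outcome is the proportion of participants with RTOG grade 3 or worse "at any time during radiotherapy and up to six weeks following completion of radiotherapy".
- **2.5 Outcomes, medication-tied window.** The next sentence reads: "The primary outcome will be assessed from randomisation until the last day of study medication use". The same end point is repeated for every secondary outcome except treatment interruption, which runs to the end of radiotherapy.
- **2.3.3 Discontinuation criteria.** Participants may be withdrawn from the study, not only from treatment, on several grounds. One is that they "experience worsening of RIOM or the emergence of other medical conditions requiring treatment that is incompatible with continued study participation". Another is drug compliance below 70% despite counselling.
- **2.4.1 (Arm A).** "Participants will be assessed weekly throughout the study duration or until complete recovery from oral mucositis, whichever occurs earlier".
- **2.4.2 (Arm B).** Weekly assessment runs "until 6week post radiotherapy or until recovery, whichever occurs earlier". The definition given is: "Recovery will be defined as Grade 0 oral mucositis on both RTOG and WHO oral mucositis scales".
- **4.3 Data management.** "Participants who discontinue or deviate from the intervention protocol will continue to be followed", and their data enter the final analysis under intention-to-treat.
- **5.2.1 Modifications.** Participants whose intervention is changed or stopped are encouraged to stay in follow-up so that outcomes can still be collected.
- **4.5 Statistical methods.** The efficacy set is a modified intention-to-treat set, "including all randomised participants who have undergone at least one post-baseline assessment".

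**The concern.** For a participant who takes study medication to the planned end, six weeks after radiotherapy, the two windows in 2.5 coincide. For one who stops earlier they do not, and nothing says which prevails. Suppose a participant stops in week 4 and first reaches grade 3 in week 6. The fixed window counts an event. The medication-tied window counts none, yet the participant stays in the 4.5 efficacy set because a post-baseline grade exists.

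The length of follow-up could then depend on tolerance, compliance and the course of mucositis itself. Timing makes this more than a technicality. Section 1.1 says mucositis usually appears after about 20 Gy and peaks at Grade 3 at 66–70 Gy, so someone who stops mid-course may well stop before a first severe grade.

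There is also a plausible difference between arms. Arm A adds three rinses and three topical applications a day, with timing restrictions, to the six benzydamine rinses that both arms use. The stopping rules in 5.2.1 are written around the Siddha medicines and study medication.

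**Working it through.** **1. Comparing the sections for a participant who stops early**

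| Question | One answer | Other answer |
|---|---|---|
| When does the primary window end? | Six weeks after radiotherapy (2.5, first sentence) | Last day of study medication (2.5, next sentence) |
| Is a discontinuer still followed? | Yes (4.3); encouraged (5.2.1) | May be withdrawn from the study (2.3.3) |
| Does recovery end assessment? | No such limit in the 2.5 definition | Yes (2.4.1, 2.4.2) |
| Who is analysed? | Intention-to-treat (4.3) | At least one post-baseline assessment (4.5) |

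An analyst cannot tell from these sections whether a first grade 3 after stopping counts.

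**2. Inputs for an illustration**

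From section 2.7: severe mucositis on benzydamine 43.6%; assumed relative reduction 15%; 20% dropout; 80 per arm. The plan's own steps: 64/(1 − 0.20) = 80, and 0.85 × 43.6% = 37.06%, a difference of 6.54 points. I take 80 per arm as given; how the 64 was derived does not affect this point.

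My assumptions, because the document gives no stopping rates by arm:
- d = share of an arm that stops study medication early. The 20% dropout figure is borrowed as a scenario; dropout and stopping medication are not the same thing.
- f = share of those participants' severe events that first occur after the stop. These are counted as non-events.
- No true effect: 43.6% in both arms.

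**3. Formulas**

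Observed risk = 0.436 × (1 − d × f).

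Two-sided 5% test with pooled variance, n = 80 per arm, D = pB − pA, p̄ = (pA + pB)/2:

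- SE0 = √[2p̄(1 − p̄)/n]
- SE1 = √{[pA(1 − pA) + pB(1 − pB)]/n}
- P(reject in favour of A) = 1 − Φ[(1.96·SE0 − D)/SE1]
- The opposite tail, Φ[(−1.96·SE0 − D)/SE1], is added for the two-sided figure.

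**4. One case in full: d = 20% in Arm A, 0% in Arm B, f = 75%**

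- pA = 0.436 × (1 − 0.15) = 0.3706; pB = 0.436; D = 0.0654; p̄ = 0.4033
- SE0 = 0.07756; SE1 = 0.07739
- (1.96 × 0.07756 − 0.0654)/0.07739 = 1.119, so the tail favouring A is 13.2%
- The opposite tail is 0.25%, so the total is 13.4%

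The observed 37.06% equals the Arm A rate that the plan's assumed effect implies.

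**5. Results with no true effect**

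| Stopping A / B | f | Observed A | Observed B | Apparent relative reduction | Two-sided rejection |
|---|---|---|---|---|---|
| 20% / 0% | 25% | 41.4% | 43.6% | 5.0% | 5.9% |
| 20% / 0% | 50% | 39.2% | 43.6% | 10.0% | 8.6% |
| 20% / 0% | 75% | 37.1% | 43.6% | 15.0% | 13.4% |
| 20% / 0% | 100% (upper bound) | 34.9% | 43.6% | 20.0% | 20.3% |
| 20% / 10% | 25% | 41.4% | 42.5% | 2.6% | 5.2% |
| 20% / 10% | 50% | 39.2% | 41.4% | 5.3% | 5.9% |
| 20% / 10% | 75% | 37.1% | 40.3% | 8.1% | 7.1% |
| 20% / 10% | 100% (upper bound) | 34.9% | 39.2% | 11.1% | 8.8% |
| 20% / 20% | any | equal | equal | 0% | 5.0% |

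**6. Equal stopping when there is a true effect**

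Taking 43.6% versus 28.6% (15 points absolute, chosen only for illustration) and 20% stopping in both arms, power at 80 per arm falls from 50.6% to 47.5%, 44.5% and 41.5% for f = 25%, 50% and 75%.

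Counting events to six weeks after radiotherapy regardless of medication sets f = 0 and removes all of these effects.

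**The case against.** The best defence is that the disputed sentence may be only loose wording. Study medication is planned in both arms until six weeks after radiotherapy, so its last day can be read as the scheduled end of the fixed window. With 4.3 and 5.2.1, events after a stop would then be collected and counted. That reading is possible, but it is not what the sentence says. The same end point is used for almost every secondary outcome, while a medication-independent one was chosen for treatment interruption. The contradiction therefore stands.

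Several stronger readings that a reader might infer are not supported:

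- **That severe events in discontinuers will be lost.** They can be lost, if the medication-tied sentence governs. A participant already at grade 3 when stopping has had the event counted.
- **That worsening mucositis or low compliance leads to withdrawal.** Section 2.3.3 is permissive, and the mucositis ground can be read as limited to cases needing treatment incompatible with the study.
- **That a grade 0 in an early week ends follow-up before the peak.** Section 2.4.1 speaks of complete recovery from mucositis, which presupposes mucositis, and Table 2 schedules RTOG grading every week from W1 to W8. What remains is narrow: a first severe episode after a genuine recovery.
- **That the modified intention-to-treat set itself loses events.** Requiring one post-baseline assessment probably excludes few people, since participants are in-patients during radiotherapy. It disagrees with the wording of 4.3, but no more than that is shown.
- **That the bias is known to favour Arm A.** The added burden makes more stopping there plausible, but no compliance or stopping rates by arm are given.

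It is also fair to say that the largest figures need all stopping in one arm and every affected event after the stop.

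**Conclusion.** The point holds as an internal contradiction about the primary-outcome window, not as proof that events will be lost. If the medication-tied sentence is followed, the endpoint is biased toward the arm with more early stopping.

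The size depends on assumed stopping rates. One-sided stopping of 20% could produce, with no true effect, up to the trial's whole assumed 15% relative reduction when 75% of the affected events follow the stop. False-positive rates would then be about 6–13% across f = 25–75%, with about 20% as an upper bound. Partly balanced stopping (20% versus 10%) does modest harm: about 5–7%, and about 9% at most. Balanced stopping leaves the test's size intact and costs power. All of this assumes that a discontinuer without a severe grade before stopping is scored as event-free.

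It should be settled now. Enrolment has begun, and grades not recorded after a stop cannot be recovered by a later analysis plan.

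**What to change.** 1. **Section 2.5.** Delete or replace the last sentence of the primary-outcome paragraph. Every randomised participant is assessed at the scheduled RTOG visits from randomisation to six weeks after radiotherapy, regardless of medication use, compliance or recovery.
2. **Sections 2.3.3, 2.4.1 and 2.4.2.** Reconcile these with 4.3 and 5.2.1, so that stopping treatment or recovering does not end outcome assessment. This concerns data collection only; when treatment is stopped is a clinical matter and is not addressed here.
3. **Section 4.5.** Align the efficacy set with the intention-to-treat statement in 4.3.

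How to handle a withdrawn participant with no later grade can be left to the statistical analysis plan.

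The cost is an amendment to the wording and some further scheduled assessments in participants who stop or recover early. It is small but not zero: Table 2 has no RTOG grade in W9–W12, and sections 4.1 and 6.5 describe follow-up after radiotherapy as by telephone. The amendment should therefore make sure that the remaining scheduled RTOG grades, including W13, are obtained in these participants too.
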